**Measurements**

[figure not shown]
**Short term main outcome is the physical activity (PA) behavior**. In parents it will be assessed with EMG, triaxial accelerometer and questionnaires. ***EMG*** will be measured using shorts with embedded textile electrodes (Suunto Oy, Vantaa, Finland / Megaelectronics Ltd., Kuopio, Finland) measuring activity from 4 thigh muscles during normal daily life and laboratory tests (Fig. 4). The measurement system has been tested for validity, repeatability and feasibility in our laboratory (Finni et al. 2007). The data is collected to a 52 g module in the waist in raw form with sampling frequency of 1000Hz. The raw EMG signal is rectified and averaged over 100 ms non-overlapping intervals. The signals are stored in a module for off line-analysis. The EMG data will be analyzed for inactivity period times and frequencies as well as for total inactivity. This analysis will be repeated using different signal levels (1%, 2%, 5% of maximum voluntary contraction) for detection of the inactivity periods. Activity histograms and on-off analysis will be performed. Burst analysis (Kern et al. 2001) will be used to quantify activity periods.

In a sub group of children we test the use of EMG shorts as measurement tool of physical activity.

Fig. 4. Shorts that are used to collect muscle EMG activity from thigh muscles.

***Acceleration.*** Triaxial acceleration will be collected during all the measurements (Alive heart monitor, Alive technologies, Australia) and be used to compare the activity counts with EMG levels for validation purposes. **In children** the PA behavior will be measured using triaxial accelerometer (Actigraf) that the children wear on their waist for one week at pre, 3, 6, 9 and 12 months after counseling intervention to parents. During this one week period, the parents will fill in diary of the childrens physical activities. In addition, children’s basic motor skills will be tested three times during the intervention.

***Questionnaires.*** From the detailed 7-day physical activity questionnaire focusing on non-exercise activity the daily MET values will be calculated for the past year at baseline and endline (modified from Lakka et al. 1997). During the days of data collection, the subjects fill in detailed physical activity diaries that reveal standing up from sitting position, walked up stairs etc.

**Long term main outcomes are health-related indices and maintenance of the behavioral change.** Venous blood samples for whole blood count, blood lipids and glucose analysis will be taken in standardized fasting conditions in the mornings 7-9 am. Samples will be analyzed using standard methods in clinical use and also metabonomics. Serum will be stored for later analysis of other health related markers such as glucose and lipid metabolism (leptin, obestatin, glucagon-like peptide, C-peptide). DNA-samples will be taken from volunteers and leucocytes extracted for further analysis of associations regarding body composition and physical performance and activity. Blood pressure will also be measured in the morning. Anthropometry including body composition (dual X-ray absorbtiometry and bioimpedance, In-Body 720, Korea) in fasting condition, hip-to-waist circumference and BMI will be measured. Subcutaneous fat thicknesses from several sites will be measured using ultrasonography.

Heart rate will be measured with the same device as acceleration. Both time domain (e.g. RMSSD, SDNN) and frequency domain (Ultralow frequency <0.0033 Hz, Very Low frequency 0.0033-0.04 Hz, Low frequency 0.04-0.15 Hz and High frequency 0.15-0.4 Hz) analysis of HR variation (HRV) will be performed (Tulppo et al. 2003). Histogram of heart rate will be constructed. Hyvinvointianalyysi (Firstbeat Technologies, Finland) will be used to identify the time of physical activity, MET and stress-related decreases in HRV. The variables will be compared with EMG data and MET levels calculated from questionnaires. High frequency band has special meaning in determining cardiovascular health. Heart rate will be measured at baseline (before and after counceling), at 6 and 12 months.

Behavioral changes will be assessed using questionnaires that include questions such as: TV/computer time usage, time and places/facilities outdoors both alone and with family, way of commute, time in sitting position, subjective energy level etc.

**Background variables.** Background information of medication, chronic and acute diseases will be assessed in the screening process. Dietary records for 3 weekdays and 1 weekend day will be kept at baseline, midline and endline to evaluate whether similar diet has been maintained during the year as assumed. Questions regarding perceived health and wellbeing are included in the questionnaires. Physical fitness will be assessed with non-exercise questionnaire.

**Field measurements during normal day.** The subjects will be well instructed for the use of HR-acceleration monitor and EMG-garments. The data will be collected continuously for waking hours during normal daily life, so that the two days of data collection are similar in all other respects except that during the second day the agreed intervention program is executed. Both days, subjects are requested to do a simple reference test containing lying down, sitting, quiet standing and stationary squat that is used to control the reproducibility of the EMG signal during the day. Each morning the data collection will be started at the laboratory by research personnel, and ended by the subject before going to bed except for heart rate recordings that will continue overnight.

**Counseling intervention.** Tailored counseling by trained research assistants will be targeted to decrease time in sitting position and increase non-exercise activity during workdays (commute and work time) and leisure time (evenings and weekends). This type of personal counseling has been shown to be effective (Leinonen et al. 2007). First, the subjects will be asked for the use of bicycle, car, elevator, stairs and walks during the day to identify items that can be modulated, e.g. standing in coffee breaks, walking about while talking to phone, taking a walk before lunch etc. Leisure time habits will be asked and changes in habits are suggested such as walk to library instead of watching TV, going to visit neighbor by foot instead of calling on the phone. The items that the subjects are willing to modify will be written down and an agreement document will be signed by the subject and researcher to confirm the intended changes in behavior. Subjects will be motivated to this change by showing graphs such as Fig.1 and explaining the importance of muscle activity and pointing out long inactivity periods when one is sitting. Counseling includes encouragement toward family physical activities during leisure time (visiting playgrounds, swimming halls, parks and forests etc.) utilizing material from www.perheliikunta.net.

The counseling will take place about after 1 week of the baseline measurements. Starting from the parent’s baseline measurement the children will wear the accelerometers for 1 week. After this there will be the counseling and after 1 week from counseling the measurements for parents wearing EMG garments will be repeated on the same weekday as the baseline measurement.

After counseling the research personnel will phone the subjects two times to ask about the compliance of the goals set and send e-mails. This reinforcement period lasts 6 months. The end measurements at 12 months are made to assess the maintenance of the habitual changes and effects on health markers. During the last 6 months there will not be researcher contact other than 9 months measurements with the subjects.

The control group will not receive the counseling intervention but will undergo the measurements similarly as the intervention group. The counseling does not include dietary counseling. The subjects will be monitored for dietary changes by questionnaires but eating habits are assumed to be maintained the same.

**Statistical analysis**. The EMG activity variables such as total inactivity time during day and mean intensity of EMG will be used to categorize people into quartiles according to 1) physical activity and 2) health marker indexes. Chi Square will be used to compare EMG distributions and levels to other variables. The difference in physiological signals between categories will be compared using One-way/Multivariate ANOVA. Correlation and regression analysis will be used to retrieve relationships between physical and health conditions and physical activity assessments. Repeated measures ANOVA will be used to determine effects of intervention complemented with mixed model ANOVA in case of missing data points.

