**Methods**

**Design.** A cluster randomized controlled intervention will be performed on parents that sit more than 50% of the work time. The intervention group will receive tailored counseling to decrease time in sitting position and increase daily activity, especially the non-exercise activity. Children aged 3-8 will be included to the study and their physical activity will be objectively monitored before and three times after the parental counseling.

**Subjects.** Eligible participants are parents with work that primarily includes sitting. *Inclusion criteria*: healthy men and women with children 3-8 years old, and having work where they sit more than 50% of their work time. *Exclusion criteria*: self-reported chronic, long-term musculoskeletal disease or progressive neurological disease, diagnosed cardiovascular or metabolic disease with regular medication, families with pregnant mother at baseline, BMI>35, children confined to a wheelchair or bed. The recruitment will be performed in Jyväskylä region delivering advertisements to parents via kindergartens and primary schools. To avoid contamination of treatment the randomization will be done regionally before recruitment and the control group will not be informed about the intervention. Both the intervention and control groups will include areas from the city center and suburbs of Jyväskylä.

**Sample size.** From the preliminary results it can be expected that small changes in behavior can effectively decrease the longest inactivity periods and total inactivity time as example in Fig.2 shows. Based on decrease in the inactivity periods by behavioral changes the sample size of 10 would be sufficient to show statistically significant changes. However, we also aim that the intervention has significant health effects. Thus, it was estimated that increase of 0.2 mmol/l in high-density lipoprotein after 6 or 12 months of intervention can be possible with the intervention. The required sample size to show this effect would be 77. Adding the cluster effect (Cambell et al. 2004) and drop-outs we estimate that 100 subjects in both groups would be needed.

Fig 2. Histogram of daily muscle activity time (% of whole day activity) divided in sections 0-5% of maximum (MVC). Women n=6, 30 measurement days, men n=6, 26 measurement days. The women performed more non-exercise activity than men and it is significantly reflected to the main outcome. **p<0,01, ***p<0,001 (Haakana 2010).

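### Secondary EMG–health analyses: quartile ANOVA and chi-square tests stand unranked beside regression on the same question, and for a weak graded relation the quartile ANOVA is the weaker test (low severity)

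*Protocol*

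**What the plan says.** All of this stands in the Statistical analysis paragraph of the protocol. It names total daily inactivity time and mean EMG intensity as examples of EMG variables, which "will be used to categorize people into quartiles according to 1) physical activity and 2) health marker indexes". Three association analyses follow:

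- Chi-square tests set the EMG data against further measures; neither the table nor its size is specified.
- For the grouped comparison the paragraph states: "The difference in physiological signals between categories will be compared using One-way/Multivariate ANOVA".
- The methods that need no grouping come last, without a rank relative to the other two: "Correlation and regression analysis will be used to retrieve relationships between physical and health conditions and physical activity assessments".

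The trial comparison is described separately: "Repeated measures ANOVA will be used to determine effects of intervention complemented with mixed model ANOVA in case of missing data points". Quartiles are not mentioned there.

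The Sample size paragraph rests on an "increase of 0.2 mmol/l in high-density lipoprotein after 6 or 12 months of intervention" and concludes that "we estimate that 100 subjects in both groups would be needed". It claims no power for the association analyses.

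**The concern.** Inactivity time and EMG intensity are measured on continuous scales. Cutting them at sample quartiles treats everyone within a quarter as alike and puts the cut-points wherever this sample's percentiles fall. An omnibus ANOVA over four groups then spends 3 degrees of freedom and ignores the order of the groups.

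This fits poorly with a question the protocol raises under Expected research results and their practical usefulness: how often and for how long inactivity has to occur before it does harm. That is a dose-response or threshold question, and a quartile boundary is not a natural place to look for a threshold.

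The same relation is also to be examined by correlation and regression. With two sets of tests and no stated priority, a reader of the results could not tell which was meant to carry the conclusion, and one of the two is often the less sensitive.

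**Working it through.** **The plan's own figure.** No power is stated for the association analyses, so there is none to reproduce. The only sample-size figure is for HDL: "The required sample size to show this effect would be 77". No SD, alpha or power is given. Read as 77 per group, with two-sided alpha 0.05 and 80% power assumed, the implied SD is 0.2 / [(1.960 + 0.842) × √(2/77)] = 0.443 mmol/l. This is plausible, cannot be verified, and says nothing about EMG–health associations.

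**Inputs.** N = 200 is 100 per group from the Sample size paragraph; N = 100 is shown as well. Assumed, because the protocol gives none of them: two-sided alpha 0.05, a bivariate normal linear relation, r from 0.15 to 0.40, and independent subjects (clustering ignored).

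**Step 1: information kept by quartiles.** For a standard normal variable the four quartile means are ±1.271 and ±0.325. Their variance is (1.271² + 0.325²)/2 = 0.861, so grouping keeps about 86% of the linear information.

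**Step 2: power.** The noncentrality is λ = N·R²/(1 − R²). R² = r² for a continuous model that contains the linear term, and R² = 0.861·r² for quartile groups. Power is the probability that a noncentral F with df and N − df − 1 degrees of freedom exceeds the 5% critical value.

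At N = 200 and r = 0.197, r² = 0.0388:

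- Continuous: λ = 200 × 0.0388/0.9612 = 8.08
- Quartiles: R² = 0.0334, λ = 200 × 0.0334/0.9666 = 6.91
- Critical F: 3.889 (1 df), 3.042 (2 df), 2.651 (3 df)

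| N | r | Linear, 1 df | Quadratic, 2 df | Spline, 3 df | Quartile ANOVA, 3 df |
|---|---|---|---|---|---|
| 200 | 0.15 | 57% | 46% | 40% | 35% |
| 200 | 0.197 | 81% | 72% | 65% | 57% |
| 200 | 0.25 | 95% | 91% | 87% | 81% |
| 200 | 0.30 | 99% | 98% | 97% | 94% |
| 100 | 0.197 | 51% | 41% | 35% | 30% |
| 100 | 0.30 | 88% | 80% | 74% | 66% |

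A simulation (3000 runs, N = 200, r = 0.20) agrees: 81% for the correlation test and 58% for quartile ANOVA. A 1-df trend over quartile scores reached 74%. Most of the ANOVA loss therefore comes from the omnibus test and less from the grouping. The protocol plans no trend test.

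**Step 3: a step instead of a line.** Simulation with 4000 runs, N = 200, and a step that explains 4% of the variance:

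| Step located at | Linear | Quadratic | Spline, 3 df | Quartile ANOVA |
|---|---|---|---|---|
| Upper quartile | 55% | 54% | 51% | 60% |
| Median | 62% | 51% | 58% | 61% |
| 1 SD above the mean | 47% | 53% | 50% | 41% |

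Quartile ANOVA holds its own when the step falls on a cut-point, and falls behind when the step lies between cut-points.

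**The case against.** The strongest objection is that the paragraph already plans regression. A reader might infer that the EMG–health question as a whole is left underpowered. The document does not support that: correlation and regression, which need no cut-points, are listed for the same question. The loss belongs to the quartile tests alone. Ranking of analyses is also commonly left to a statistical analysis plan, which is not shown here. This stands, and it is a main reason for the low severity.

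A reader might also infer that the trial's conclusions are at risk. They are not. The three listed hypotheses concern the effect of counseling on parents' activity, lasting behavioural and health change, and transfer to the children. They are tested by repeated measures or mixed model ANOVA without quartiles. The harmful-inactivity question appears as an aspiration under expected results and is not one of those hypotheses.

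A large loss for chi-square is tempting too. If one assumes a 4 × 4 quartile table, simulation gives about 33% power at N = 200 and r = 0.20. The protocol states no table size, however, and the other variables may be naturally categorical, so that figure does not describe this plan.

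Two further points stand. The gap between 81% and 57% compares quartiles with a purely linear test; against the nonlinear model recommended below it is about 8 to 15 points. And the quartile sentence is unclear about which variable is cut. It can be read as grouping people by activity or health and comparing EMG or heart rate signals as continuous outcomes.

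What the objection does not remove is that quartile tests are written into the plan as tests, beside a method that is usually at least as sensitive for a graded relation.

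**Conclusion.** The point holds at low severity and for the secondary, associational analyses only. At N = 200 with an assumed weak linear relation (r about 0.2, clustering ignored), quartile ANOVA has about 57% power, against about 81% for a linear continuous test and 65 to 72% for a nonlinear one. At r = 0.30 the figures are 94% against 99%, so little is lost at that N. If the relation is a step at a quartile boundary there may be no loss at all. The correlation, linearity and independence are assumptions, and the effect on the chi-square tests cannot be sized. Nothing here bears on the randomised comparison or on the sample size.

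**What to change.** State that regression on the continuous EMG variables, with one prespecified nonlinear term (quadratic or spline), is the main analysis of EMG against health markers. Use quartiles for descriptive tables only, and do not offer quartile ANOVA or chi-square p-values as evidence for these associations. If quartiles stay in the tables, say plainly which variable is cut.

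This changes a few sentences and needs no new data. The results become slightly less simple to present, and some power is given up if the true relation is a sharp step at a cut-point.

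### Regions are randomised, but the named test of the intervention effect, repeated measures ANOVA, does not account for region; if outcomes correlate within regions, between-arm errors are understated

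*Protocol*

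**What the plan says.** Under Methods, the Design paragraph states: "A cluster randomized controlled intervention will be performed on parents that sit more than 50% of the work time". The Subjects paragraph gives the unit of allocation: "the randomization will be done regionally before recruitment". It also says: "Both the intervention and control groups will include areas from the city center and suburbs of Jyväskylä". Each arm therefore holds more than one area, but the number is not given.

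The Sample size paragraph starts from an assumed "increase of 0.2 mmol/l in high-density lipoprotein after 6 or 12 months of intervention" and continues: "The required sample size to show this effect would be 77". It then adds: "Adding the cluster effect (Cambell et al. 2004) and drop-outs we estimate that 100 subjects in both groups would be needed". The source cited there is the CONSORT extension to cluster trials.

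The Statistical analysis paragraph, which closes the part on measurements and counselling, has one sentence on the effect of the intervention: "Repeated measures ANOVA will be used to determine effects of intervention complemented with mixed model ANOVA in case of missing data points". No region term, cluster-level analysis or cluster-robust standard error appears anywhere in the protocol.

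**The concern.** The sample size paragraph and the analysis paragraph rest on different views of the data. The first accepts that people from one region resemble each other and that this costs information. The second names a test whose between-person error term treats every participant as independent.

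People in one region share kindergartens and schools (the recruitment route), outdoor facilities and travel conditions, so correlated changes in activity are plausible. If they occur, the variation between regions enters the difference between arms but not its standard error. P-values are then too small and confidence intervals too narrow. The degrees of freedom are wrong as well: they come from about 200 people, when only the regions were randomised.

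This touches every hypothesis that is judged by comparing arms, including the health markers at 6 and 12 months and the children's activity.

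**Working it through.** **The plan's own figure.** The 77 cannot be reproduced, because the SD, significance level, power and basis (per arm or total) are not given. It can only be solved backwards. With n per arm = 2 × (SD/0.2)² × (1.96 + 0.84)², two-sided 5% and 80% power, 77 per arm needs an SD of 0.443 mmol/l. With 77 as a total it needs 0.313.

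If 77 and 100 are on the same basis, the joint allowance for clustering and drop-out is 100/77 = 1.30. Two readings of that factor:

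- All of it is design effect: error = 2 × (1 − Φ(1.96/√1.30)) = 2 × (1 − Φ(1.72)), about 8.5%.
- Drop-out is 10% (assumed): design effect = 100 × 0.9/77 = 1.17, and error = 2 × (1 − Φ(1.96/√1.17)), about 7.0%.

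So any part of the 1.30 that is meant for clustering implies an error above 5% under the named test.

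**Inputs for the range.** The following are assumptions:

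- 100 people per arm, which is one reading of the protocol's figure
- 2 to 20 regions per arm
- ICC of the change score 0.01 to 0.05
- a two-sided 5% level

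**Formulas.** With k regions per arm, m = 100/k people per region. Design effect DE = 1 + (m − 1) × ICC. True standard error over reported standard error = √DE. True two-sided error = 2 × (1 − Φ(1.96/√DE)).

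Example with k = 4 and ICC 0.02: m = 25, DE = 1 + 24 × 0.02 = 1.48, √DE = 1.22, error 10.7%.

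| Regions per arm | People per region | DE at ICC 0.01 / 0.02 / 0.05 | True error at ICC 0.01 / 0.02 / 0.05 |
|---|---|---|---|
| 2 | 50 | 1.49 / 1.98 / 3.45 | 10.8% / 16.4% / 29.1% |
| 4 | 25 | 1.24 / 1.48 / 2.20 | 7.8% / 10.7% / 18.6% |
| 7 | 14.3 | 1.13 / 1.27 / 1.66 | 6.6% / 8.1% / 12.9% |
| 10 | 10 | 1.09 / 1.18 / 1.45 | 6.0% / 7.1% / 10.4% |
| 20 | 5 | 1.04 / 1.08 / 1.20 | 5.5% / 5.9% / 7.4% |

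Over this table √DE runs from 1.02 to 1.86. If 100 is the total (50 per arm), region sizes halve for the same k. Two regions per arm then have 25 people each, and the row for 4 regions applies.

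**Simulation check.** With two time points, the group-by-time test equals a t-test on the change. It was simulated 20,000 times per setting for 2, 4, 7 and 10 regions per arm. At ICC 0.05 the individual-level test rejected in 29.7%, 18.8%, 12.8% and 9.8% of runs, close to the formula. At ICC zero it rejected in 4.8% to 5.0%. A t-test on region means held 4.6% to 5.3% throughout.

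**Degrees of freedom.** An individual-level test with 200 people has 198 (critical t about 1.97). A region-level test has 2k − 2: 6 for four regions per arm (critical t 2.45) and 2 for two regions per arm (critical t 4.30).

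**The case against.** The strongest reply is that the analysis plan is not shown and that random-effect structures are usually specified there. The authors cite the cluster extension of CONSORT, so they knew of the issue, and the lack of a region term is read from silence. This stands only in part. The protocol does not leave the test open: it names one, and the only reason it gives for a mixed model is missing data.

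The second reply stands in full. The inflation depends on a positive ICC, and its size on the number of regions. With an ICC of zero there is none, and with many small regions it is slight. The protocol states no significance level, so 5% is convention.

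Four stronger readings are tempting but not supported:

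- A reader might infer that the chi-square and one-way or multivariate ANOVA analyses are also faulty tests between arms. The Statistical analysis paragraph uses them for activity and health categories and for relations with other variables. They are not part of this point.
- A reader might infer that both parents or several siblings enrol and add a family level. The Subjects paragraph neither plans nor excludes this, so it is a condition to check.
- A reader might infer a balanced or stratified allocation by city centre and suburb that the model must reflect. The protocol says only that both arms will include areas of each kind. A fixed effect for area type is optional.
- A reader might take the short-term muscle-activity outcome as certainly affected. The Protocol paragraph limits which measurements controls attend, while the Counseling intervention text says they are measured like the intervention group. The point applies to that outcome only if arms are compared on it.

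**Conclusion.** The concern holds in conditional form. The only sentence on testing the intervention effect ignores the unit of randomisation and conflicts with the protocol's own sample size reasoning. This is a rule fixed badly, not a detail left for later.

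It cannot be said that the error rate is wrong by a known amount. The figures run from close to nominal (5.5%, with 20 regions per arm and ICC 0.01) to very large (29.1%, with 2 regions per arm and ICC 0.05). All of them rest on assumed ICCs, assumed numbers of regions, 100 people per arm and a conventional 5% level. Because the protocol itself allows for clustering in the sample size, assuming an ICC of zero would not be consistent with it.

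**What to change.** Replace the last sentence of the Statistical analysis paragraph with wording such as:

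> Between-arm effects on parent and child outcomes will be estimated with a method that accounts for region, the unit of randomisation. This will be a linear mixed model for the repeated measurements with a random effect for region and small-sample degrees of freedom based on the number of regions or, if regions are few, an analysis of region-level summaries. A random effect for family will be added if more than one parent or child per family takes part.

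In the Sample size paragraph, state the number of regions per arm and the assumed ICC, since the choice between the two methods depends on them.

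The change is a few sentences, plus keeping each participant's region in the analysis file. The statistical cost is wider intervals. Relative to the individual-level interval, the width grows by √DE times the ratio of critical values. At ICC 0.01 this is 1.11 × 2.45/1.97, about 1.4, with four regions per arm, and 1.22 × 4.30/1.97, about 2.7, with two. With two regions per arm, adding a term for area type would leave 1 degree of freedom (critical t 12.7), so that term should not be required. If the trial has so few regions, it is better to know this before the data are analysed.

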**Ethics.** We will submit the study plan with questionnaires and informed consent for evaluation by the local ethics committee. The RCT will not begin before approval has been received. Subjects will be volunteers with right to withdraw from the study at any time without consequences. The study will be conducted according to good scientific practice.

**Protocol.** The protocol of the study is shown in Fig. 3. Before counseling the parents will be measured for baseline data (fasting blood samples, anthropometry, questionnaires, physical fitness test) and a representative normal day EMG activity with other measures of physical activity level. After counseling the representative day with agreed behavioral changes will be measured again using EMG and other devices for physical activity level assessment. In the first 3 months the compliance will be reinforced by phone calls and possible modifications to the agreed intervention will be made. Between 3 to 6 months the compliance will be followed once a month and no contact with the subjects will be made in the maintenance period. The midline and endline measurements include fasting measurements, questionnaires and 24-hour heart rate recordings. Control group participates only in baseline and normal day measurements, midline and endline measurements. Children will be measured at baseline, after 3, 6, 9 and 12 months for physical activity behavior using triaxial accelerometers (Actigraf).

Figure 3. Timeline of the project showing the timing of physical activity (PA) measurements for parents and children.

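### The only intervention test named, repeated measures ANOVA without a baseline covariate, gives up precision on the two-day EMG outcome and probably on the others

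*Protocol*

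**What the plan says.** The Statistical analysis paragraph gives the intervention test in one sentence: "Repeated measures ANOVA will be used to determine effects of intervention", with a mixed model version added where data are missing. It does not state which visits are the repeated levels, which term is the effect, or any covariate. Regression appears in the same paragraph, but only for relating health and physical condition to activity assessments.

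The main outcomes all have a baseline value:

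- **Parents, health markers.** Baseline is taken before the intervention: "Before counseling the parents will be measured for baseline data (fasting blood samples, anthropometry, questionnaires, physical fitness test". Later visits follow at midline and endline (6 and 12 months): "The midline and endline measurements include fasting measurements, questionnaires and 24-hour heart rate recordings".
- **Parents, EMG.** There is one day before counseling and one after it, on the same weekday. The field-measurement paragraph intends that "the two days of data collection are similar in all other respects except that during the second day the agreed intervention program is executed".
- **Children.** "Children will be measured at baseline, after 3, 6, 9 and 12 months for physical activity behavior using triaxial accelerometers".

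On allocation, the Subjects paragraph says that "the randomization will be done regionally before recruitment and the control group will not be informed about the intervention". On sex, the legend to Fig. 2 reports: "The women performed more non-exercise activity than men and it is significantly reflected to the main outcome".

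The text is not consistent on whether controls have a second EMG day. The Protocol paragraph under Methods limits controls to baseline, normal-day, midline and endline measurements. The text just before the Statistical analysis paragraph says that controls are measured in the same way as the intervention group.

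**The concern.** When baseline is one of the repeated values, the group-by-time test compares changes from baseline. A change score fixes the slope on baseline at 1 and so carries the full baseline noise into the effect estimate. Using the same baseline value as a covariate lets the data set the slope, and for any correlation below 1 this gives a smaller variance. The loss is greatest where visits correlate weakly, which is plausible when a single day of EMG is compared with another single day. The baseline values are collected anyway, so the precision is given up for nothing.

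**Working it through.** **1. Inputs.** The test and the visit schedule come from the protocol as set out above. The correlation r between baseline and follow-up is not in the documents, so a range of 0.3 to 0.9 is assumed. Variances are taken as equal across visits and participants as independent, so clustering is ignored.

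**2. The plan's own figure.** The Sample size paragraph gives 77 for a 0.2 mmol/l rise in HDL. This cannot be reproduced, because SD, alpha, sidedness, power and r are not given. If 77 is per arm, at two-sided 5% and 80% power, the implied SD is 0.2 × √(77/2) / 2.80 = 0.443 mmol/l. That value only sets the scale of the simulation in step 6.

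**3. What the test is.** With two EMG days and two arms, the repeated factor has only the levels before and after. The group-by-time F is then the square of a t-test on change scores. With HDL at 0, 6 and 12 months, group-by-time has 2 degrees of freedom and also covers 6 against 12 months. With five visits in the children it has 4. For these outcomes the wording would also fit a repeated factor of follow-up visits only.

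**4. Variance for one follow-up**, in units of 2·SD²/n per arm. The change score has 2(1−r), the baseline-adjusted estimate has 1−r², and their ratio is (1+r)/2.

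| r | change score | adjusted | ratio | 1/ratio |
|---|---|---|---|---|
| 0.3 | 1.40 | 0.91 | 0.65 | 1.54 |
| 0.5 | 1.00 | 0.75 | 0.75 | 1.33 |
| 0.7 | 0.60 | 0.51 | 0.85 | 1.18 |
| 0.8 | 0.40 | 0.36 | 0.90 | 1.11 |
| 0.9 | 0.20 | 0.19 | 0.95 | 1.05 |

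The last column is the factor by which participants would have to rise for the change score to match the adjusted estimate.

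For the mean of two follow-ups with one common correlation, the change score has (1+r)/2 + 1 − 2r and the adjusted estimate has (1+r)/2 − r². At r = 0.7 that is 0.36/0.45 = 0.80, and at r = 0.9 it is 0.14/0.15 = 0.93. These figures describe a contrast of mean follow-up with baseline, not the 2-df test.

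**5. Power for one follow-up.** A change-score test with 80% power has noncentrality 1.96 + 0.84 = 2.80. At r = 0.4 (ratio 0.70), 2.80/√0.70 = 3.35, and 3.35 − 1.96 = 1.39, which is about 92% power. At r = 0.7, 2.80/√0.85 = 3.04, and 3.04 − 1.96 = 1.08, which is about 86%.

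**6. Bias.** In 8,000 simulated individually randomised trials (r = 0.7, 77 per arm, true effect 0.200), both analyses averaged 0.201, with a variance ratio of 0.86 (theory 0.85). Two kinds of baseline gap then have to be kept apart:

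- **Chance gap.** The change score shifts by (1−r) times the gap, in the opposite direction. For a 0.1 mmol/l gap at r = 0.7 this is 0.3 × 0.1 = 0.03 mmol/l. The simulated slope on the gap was −0.29 for change scores and 0.01 with the covariate.
- **Stable difference between the arms' areas.** The change score is unbiased. The baseline-adjusted estimate is off by (1−r) times the gap, again 0.03 mmol/l for 0.1 at r = 0.7.

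**The case against.** Repeated measures ANOVA is a valid and conventional choice, and preferring baseline adjustment is mainly a matter of efficiency. That is right, and it limits the point. Five further objections deserve an answer.

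- **Baseline as a repeated outcome throughout.** A reader might infer that the protocol specifies this for every outcome. It does not. The schedule forces it for EMG only; for blood markers and child accelerometry it is an inference from the absence of a covariate.
- **Regression to the mean.** A reader might infer that baseline differences between arms will bias the planned analysis. The documents do not support this. The shift arises only from a chance imbalance. Allocating regions before recruitment can instead produce stable differences, and there the covariate model is the one that is off. A chance gap as large as 0.3 SD is also uncommon with 100 per arm: 0.3/√(2/100) = 2.1 standard errors, ignoring clustering.
- **Correlation.** No r is documented. The EMG days are meant to match in weekday and circumstances, so r may exceed 0.3 to 0.5 and the gain would then shrink. The Sample size paragraph also considers 10 subjects enough for the inactivity outcome, so precision is least scarce there. HDL drives the sample size, and the gain is smaller if its r is 0.7 or more.
- **Clustering.** The ratios assume independent participants. Between-area variance need not fall by (1+r)/2.
- **Control EMG day.** If controls have no second day, neither the change-score test nor its replacement exists for EMG.

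All five stand as limits. None removes the core: the only named test of the intervention uses no baseline covariate.

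**Conclusion.** The point holds as a loss of precision. It is firm for the two-day EMG outcome, provided controls have a second EMG day. For blood markers and children's accelerometry it is the likely reading but is not stated, and the group-by-time test there has several degrees of freedom. For one follow-up, baseline adjustment saves 25% to 35% of the change-score variance if r is 0.3 to 0.5, and 5% to 15% if r is 0.7 to 0.9. These sizes rest on an assumed r, equal variances and no clustering. They do not show that the planned analysis is biased, and baseline adjustment would not reliably remove stable regional differences between the arms.

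**What to change.** Replace the sentence on the intervention test with one to this effect:

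*The intervention effect is estimated in a linear mixed model of the post-baseline values (EMG day 2; parents at 6 and 12 months; children at 3, 6, 9 and 12 months). Fixed terms are arm, visit, arm-by-visit, the participant's own baseline value of that outcome, baseline-by-visit, and sex. Random effects are the randomised area, family where relevant, and participant where there are repeated follow-ups. The effect is the adjusted arm difference at the named visit.*

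With a single post-baseline EMG day the visit terms and the participant effect drop out. Sex is included because the protocol's own Fig. 2 ties it to the main outcome. The area effect is needed because areas, not parents, are randomised.

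Keep the change-score analysis as a sensitivity analysis. If the two results differ, the direction of the baseline gap and the way parents were recruited in each area should be discussed, because a stable gap leaves (1−r) times its size in the adjusted estimate.

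Reconcile the two statements on control measurements so that it is clear whether controls have a second EMG day.

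The cost is one changed sentence and one additional sensitivity analysis. If the control measurements already include the second EMG day, no new data, visits or participants are needed.
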